| **Criteria for evaluation:**  Treatment will be initiated on study Day 1.  Primary outcome:   - The change from baseline in PN calories, assessed weekly throughout the study.   Secondary outcome:   - The change from baseline in body weight (weight-for-age z-score), assessed weekly throughout the study.   Safety outcomes:   - The incidence of adverse events, grade 2 or higher. All adverse events will be reported by study participants including changes in stool consistency (Bristol scale)/amount/frequency (if applicable), increased ostomy output (if applicable, defined as >2.5 mL/kg/hour), the need to decrease enteral feeds, changes in urine color assessed by Dehydration Color scale and discontinuation from the study treatment, assessed over the entire study from baseline until Day 90. - The incidence of abnormalities in vital signs (blood pressure, pulse rate, respiratory rate, temperature) assessed at baseline, Day 7, 14, 28, 60, and 90. - The incidence of abnormalities in hematology and biochemistry parameters, based on Boston Children’s Hospital reference ranges, assessed at baseline, Day 7, 14, 28, 60, and 90.   Exploratory outcomes:   - The change from baseline in 72-hour fecal fat and coefficient of fat absorption, assessed at baseline (Days -3 to -1) and prior to the end of the study (Days 87-89). - The change from baseline in plasma fatty acid composition and fat-soluble vitamins (A, D, E, and K), assessed at Day 7, 14, 28, 60, and 90. - Change in growth height (assessed by height-for-age Z-score) and head circumference (assessed by head-circumference-for-age z-score) [in subjects < 36 months]) from baseline, assessed at Day 7, Day 14, Day 28, Day 60, and Day 90 - The change in BMI z-score assessed at Day 7, 14, 28, 60, and 90. - The change from baseline in PN volume, assessed weekly. - The change from baseline in total enteral calories and total enteral volume, assessed weekly. - The change from baseline in total oral calories and total oral volume, assessed weekly. - The ability to wean from PN, assessed over the entire study from baseline until Day 90. | |

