# INTRODUCTION

## BACKGROUND

Short bowel syndrome (SBS) is a rare condition included in The National Organization for Rare Disorders (NORD) database. The estimated prevalence of SBS in adults in the US is reported to be approximately 10,000-20,000 individuals (Oley Foundation [www.oley.org]; Short Bowel Syndrome Foundation [http://www.shortbowelfoundation.org]), affecting males and females in equal numbers. The disorder has numerous causes, both congenital and acquired, but a common etiological factor is the functional or anatomical loss of extensive segments of the small intestine, leading to a severe decrease in intestinal absorptive capacity. In children, the most common causes are necrotizing enterocolitis, intestinal atresias, and intestinal volvulus.^1^

The link between intestinal loss of the small bowel and the risk of SBS is self-evident. Losing large amounts of the small intestine compromises the digestive and absorptive processes. Adequate digestion and absorption cannot take place and proper nutritional status cannot be maintained. Treatment of SBS is focused on supplying the nutrients and vitamins that patients lack and may include (1) a high-calorie diet that includes vitamins, minerals, carbohydrates, proteins, and fats; (2) injections of vitamins and minerals; (3) administration of drugs that slow down the normal movement of the small intestine; and (4) feeding through a vein (i.e., parenteral nutrition (PN)).

Most SBS patients are initially fed with PN. In some patients, intestinal adaptation, alone or in combination with dietary modifications, allows weaning from PN. Unfortunately, many patients cannot be weaned from PN because of dramatically reduced intestinal length or function. Patients on long-term PN frequently experience serious metabolic complications. Most complications are hepatic and biliary disorders manifested by hepatic steatosis, fibrosis and cholestasis.[^1^](#_REFERENCES) These disorders can progress to fulminant liver failure.[^1^](#_REFERENCES) Before 2006, advanced liver disease was the most common cause of death in SBS patients.[^2^](#_REFERENCES) In infants with SBS, PN-associated liver disease (PNALD) is estimated to occur in 40-60% of those receiving long-term PN[^3,4^](#_REFERENCES) with mortality estimated to be as high as 80%.[^5,6,7^](#_REFERENCES)

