Many consider PNALD to be caused in part by the intravenous lipid emulsions used to provide fat calories in the PN formulation, although the etiology is unclear.[^3,4,8^](#_REFERENCES) It has been suggested that PNALD may be caused by inflammation that is related to the type of intravenous lipid emulsion used.[^4,8^](#_REFERENCES) These fat emulsions cannot be eliminated from PN because by doing so would lead to the development of essential fatty acid deficiency and its concomitant complications.[^8,9^](#_REFERENCES) Recent data has shown that the replacement of a primarily omega-6 soybean oil lipid emulsion with those comprised primarily of omega-3 fatty acids may lead to reduction or avoidance of PNALD without predisposing the patient to essential fatty acid deficiency.[^3,10^](#_REFERENCES) Moreover, having a more bioavailable form of essential fatty acids that can be administered enterally may reduce or avoid the need for intravenous lipid emulsions entirely.

Although increased and earlier enteral feeding may reverse PNALD, data suggests that duration of hepatic dysfunction can last for several months after cessation of PN.[^11,12,13^](#_REFERENCES) In one retrospective study, children with a history of PNALD who have achieved PN independence had persistent alanine aminotransferase (ALT) elevations despite normalization of direct bilirubin concentrations. This suggests that hepatic injury may be ongoing beyond the time of bilirubin normalization.[^13^](#_REFERENCES) PN-dependent infants can achieve normalization of marked hyperbilirubinemia with enteral nutrition, however this improvement in liver function usually begins only after full enteral nutrition is tolerated and PN is withdrawn. These findings support the aggressive weaning of PN to enteral nutrition in infants with SBS. ^12^

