# STUDY DESIGN

## BASIC DESIGN CHARACTERISTICS

This study is a phase 3, open labeled uncontrolled single center,
clinical trial to determine the safety, tolerability, and bioavailability of the RELiZORB enzyme cartridge with enteral nutrition when used daily for a total 90 days of treatment when given to pediatric subjects with SBS, aged 2 years – 18 years, who have been PN dependent for at least 6 months.

Subjects with a signed informed consent will be enrolled in the study. Results from screening must not show any clinically significant abnormalities in order for the subject to progress to the enrollment and treatment phases of the trial. During the screening visit, subjects and legal guardians will also receive education from a registered dietician on recording caloric intake and composition in oral and enteral feeds, and PN. As part of this education, the subject and parent/guardian will receive access to a nutrition/food tracking phone application (Cronometer) to assist them with this task throughout the study. If there is no electronic capability, a paper diary will be provided. The subject and parent/guardian will also receive education from a registered nurse on accurate and complete stool collection. Subjects will be provided with a standardized weight scale for at-home weight recording.

Upon completing screening and enrollment, subjects and their legal guardians will be instructed to record total calories and composition in oral and enteral feeds and TPN and to collect all stool for 72 hours (Days -3 to -1) prior to the first day of treatment. The stool collection and recording will be repeated in the 72-hours preceding the final study visit (Days 87-89). All stool will be collected in a single container and kept refrigerated during collection. If necessary (for example, out of state participants, excessively watery stools), subjects will be admitted to our dedicated research center during this collection period.

On the first day of treatment (Day 1), all subjects will use the RELiZORB enzyme cartridge to administer their enteral nutrition and will continue to use a cartridge daily for a total of 90 days. The study device will be used with enteral nutrition administered to the subject daily by a parent or guardian for 90 days (Day 1 to Day 90).

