### Exclusion Criteria

To be eligible for entry into the study, the subject must not meet any of the exclusion criteria listed below:

1. Other causes of chronic liver disease other than SBS (i.e. hepatitis C, cystic fibrosis, biliary atresia, alpha 1 anti-trypsin deficiency, and Alagille syndrome).
2. The patient has had a bowel lengthening procedure, including but not limited to, a STEP procedure.
3. Any serum triglyceride concentration >400 mg/dL at screening.
4. Pancreatic insufficiency as defined as the use of pancreatic enzymes within 30 days prior to screening.
5. Evidence of untreated intestinal obstruction or active stenosis, as determined by the investigator.
6. Unstable absorption due to cystic fibrosis or known DNA abnormalities (i.e., familial adenomatous polyposis, Fanconi syndrome) as determined by the investigator.
7. History of microvillus inclusion disease, as determined by medical history.
8. Severe known dysmotility syndrome (i.e., pseudo-obstruction, gastroschisis-related motility disorders), as determined by the investigator.
9. Initiation of teduglutide or other GLP-2 analogues within 6 months of screening
10. Use of growth hormone, or supplemental glutamine within 3 months prior to screening.
11. Use of cisapride within 30 days prior to screening.
12. Active clinically significant pancreatic or biliary disease, as determined by the investigator.
13. Receiving enteral nutrition via any formula that is not compatible with the RELiZORB cartridge (for example, insoluble fiber-containing formulas).
14. Determined by the investigator to be unsuitable for participation in this trial for any reason.

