### Safety endpoints

The safety endpoints include:

- Subject incidence of adverse events, including changes in stool consistency assessed by Bristol scale, changes in stool amount/frequency (if applicable), increased ostomy output (if applicable, defined as >2.5 mL/kg/hour), the need to decrease enteral feeds, changes in urine color assessed by Dehydration Color scale, and discontinuation from the study treatment.
- Subject incidence of abnormalities in vital signs, assessed at baseline, Day 7, 14, 28, 60, and 90.
- Subject incidence of abnormalities in hematology and biochemistry parameters assessed at baseline, Day 7, 14, 28, 60, and 90.

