| Clinical laboratory evaluations^d^ | X |  |  |  | X |  | X |  | X |
| Dietician Education | X |  | X |  | X |  | X |  | X |
| 72-hour fecal collection^e^ |  | X |  |  |  |  |  |  | X (final visit) |
| Lipid profile^f^ | X |  |  |  | X |  | X |  | X |
| Total plasma FAs^g^ | X |  |  |  | X |  | X |  | X |
| Liver tests^h^ | X |  |  |  | X |  | X |  | X |
| Nutritional assessment | X |  | X |  | X |  | X | Weekly | X |
| Record nutritional intake^i^ |  | Daily | X | Daily | X | Daily | X | Daily | X |
| Change in PN/ enteral feeding | X | X | X |  | X |  | X | Weekly | X |
| Home Body weight (WAZ) |  |  |  |  |  |  |  | Weekly |  |
| RELiZORB |  |  | X | Daily | X | Daily | X | Daily | X |
| Adverse Events^j^ |  |  | X | Daily | X | Daily | X | Daily | X |
| Concomitant Medications |  |  | X | Daily | X | Daily | X | Daily | X |
| Assess medical/ surgical procedures | X |  | X |  |  |  | X |  | X |
| Supply Investigational Product |  |  | X |  | X |  | X |  | X |
| Review Daily Patient Diary |  |  |  |  | X |  | X | Weekly | X |

I/E criteria = Inclusion and exclusion criteria.

FAs =fatty acids.

PN = Parenteral nutrition.

^a^ Record known bowel length/type from last surgical resection or other measurement.

^b^ Blood pressure, pulse rate, respiratory rate and temperature.

^c^ Includes height or length, head circumference (for subjects < 36 months), and weight. If a physical examination or nutrition assessment was performed during the 3-day screening period, it will be used for the baseline assessment when available.

^d^ Includes chemistry (including fat-soluble Vitamins A, D, E, and K), hematology, coagulation and C-reactive protein (CRP). Clinical laboratory evaluations obtained at time of screening will serve as the baseline assessment.

^e^ 72-hour fecal collection will occur in the 72 hours preceding treatment day 1 and the final clinic visit day 90

^f^ Samples of the lipid profile will include cholesterol, high-density lipoprotein (HDL), very low-density lipoprotein (VLDL), and low-density lipoprotein (LDL). Results of samples obtained at time of screening will be analyzed during enrollment period, prior to participant receiving device.

^g^ Samples of total plasma fatty acids will include total saturated, total monosaturated, total polyunsaturated, total Omega-3, total Omega 6, total fatty acids, a-linolenic Acid, linoleic acid, oleic acid, EPA, arachidonic acid, mead acid, DHA, and triene:tetraene ratio.

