### Safety Analysis

Safety analysis will be performed on all subjects enrolled in the study with a follow-up safety assessment. Adverse event data will be listed individually and summarized by system organ class and preferred terms within a system organ class. The number and percentage of subjects with adverse events (AEs), serious adverse events (SAEs), AEs that lead to discontinuation, study device-related AEs (determined by investigator), and AEs that lead to death will be summarized. Only AEs grade 2 or higher will be presented. When calculating the incidence of adverse events, each adverse event will be counted only once for a given subject. If the same adverse event occurs on multiple occasions in a subject, the occurrence with the highest severity and relationship to study device will be reported. If two or more adverse events are reported as a unit, the individual terms will be reported as separate events. AEs will also be summarized with regards to severity and relation to study drug. Additionally, the frequency of each AE within-subject will be calculated and summarized across all subjects in order to rank the commonality of each particular AE.

Vital signs, hematology, and clinical chemistry parameters from baseline to the end of the study will be presented as outlined above for continuous outcomes and reported to the DSMB at the regularly scheduled meetings. Incidence of changes in laboratory parameters from normal to abnormal, based on Boston Children’s Hospital reference ranges, will be identified and lab values listed by subject.

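### The stated laboratory incidence rule counts changes from normal to abnormal, which is narrower than the safety endpoint it is meant to report

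*Protocol*

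**What the plan says.** Section 3.3.3 defines the endpoint as "Subject incidence of abnormalities in hematology and biochemistry parameters assessed at baseline, Day 7, 14, 28, 60, and 90". The synopsis outcome reads "The incidence of abnormalities in hematology and biochemistry parameters" and adds that the hospital's reference ranges apply. Neither restricts the endpoint to children who were in range at entry, and both list baseline among the assessments.

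The analysis text differs. Section 10.2.3 and the synopsis statistical methods both say that "Incidence of changes in laboratory parameters from normal to abnormal" will be identified, against the same ranges. Laboratory values are also to be summarised as continuous outcomes and listed by subject.

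On the starting point, Table 2 footnote d says: "Clinical laboratory evaluations obtained at time of screening will serve as the baseline assessment". On entry, section 3.1 says: "Results from screening must not show any clinically significant abnormalities". Inclusion criterion 7 in section 3.2.1 accepts a direct bilirubin outside the range if the investigator judges it not clinically significant. The eligibility criteria set no limit on ALT, AST or GGT. Exclusion criterion 1 covers "Other causes of chronic liver disease other than SBS", so liver disease due to short bowel syndrome itself is not excluded by that criterion.

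**The concern.** An incidence count should answer the endpoint it reports. Here the endpoint asks how many children had abnormal values, while the rule asks how many moved from normal to abnormal. The two agree only if nobody starts out of range, and the entry criteria do not ensure that.

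The background makes abnormal liver values at entry plausible. It states that "PN-associated liver disease (PNALD) is estimated to occur in 40-60% of those receiving long-term PN", although that figure is for infants, and it cites "persistent alanine aminotransferase (ALT) elevations despite normalization of direct bilirubin concentrations", although that was in children already off parenteral nutrition. Both are indirect for this trial.

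What is at stake is how the laboratory safety result reads. With no control arm, a low count could be taken to mean that few children had abnormal or worsening values, when some could not have been counted unless they first returned to range.

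**Working it through.** **1. Rule and endpoint side by side, for one parameter in one child**

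| Course | Counted by the 10.2.3 rule | Abnormal under the endpoint |
|---|---|---|
| In range throughout | No | No |
| In range at screening, out of range later | Yes | Yes |
| Out of range at screening and every visit, stable | No | Yes |
| Out of range at screening and every visit, worsening | No | Yes |
| Out of range at screening, in range Day 14, out again Day 28 | Arguably yes | Yes |

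The mismatch lies in the third and fourth rows. The fourth matters for safety.

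**2. The protocol's own figures for a proportion (section 10.2.5)**

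The formula is p ± 1.96 × √(p(1 − p)/32). For p = 0.20 it gives 0.20 ± 0.139, or 0.06 to 0.34. For p = 0.50 it gives 0.33 to 0.67, and for p = 0.80 it gives 0.66 to 0.94. All three match the text. They take 32 as the denominator, and this point changes none of them.

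**3. How the two counts separate (illustration, not an estimate of size)**

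The protocol does not give the share q of children out of range at screening. Assume q from 0 to 50%, that 20% of children in range at screening later go out of range, and that those out of range stay there.

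- Rule: 0.20 × 32 × (1 − q)
- Any post-baseline abnormality: 32q + 0.20 × 32 × (1 − q)

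| q | Rule | Any post-baseline abnormality |
|---|---|---|
| 0% | 6.4 | 6.4 |
| 10% | 5.8 | 9.0 |
| 25% | 4.8 | 12.8 |
| 50% | 3.2 | 19.2 |

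As q rises, the rule's count falls while the endpoint's count grows. They agree only at q = 0.

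**4. Denominator**

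At q = 25%, 4.8 children are 15% of all 32 but 20% of the 24 who were in range at screening. Section 10.2.3 names a general set for safety analysis and 10.2.4 defines a different safety population. Neither says which of these two denominators the laboratory count uses.

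**5. Why a shift table alone is not enough**

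Take a hypothetical child with ALT at 2 × ULN at screening that rises 8.5-fold, to 2 × 8.5 = 17 × ULN. This exceeds the 8-fold stopping limit in section 9.10. The normal-to-abnormal count is 0, and a shift table shows only high to high.

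The time-weighted average in 10.2.2 does not supply a count either. With a ratio of 8.5 at one clinic visit and 1 at the other four, over the 83 days from Day 7 to Day 90:

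- Peak at Day 7: 1 + 7.5 × (0.5 × 7)/83 = 1.32
- Peak at Day 60: 1 + 7.5 × (0.5 × 62)/83 = 3.80

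The peak itself would still show in the by-visit maximum and in the listing.

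**The case against.** The strongest reply has four parts.

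- **Incidence usually means new occurrence.** In an uncontrolled trial, counting abnormalities that were present before the device was used would make entry status look like a treatment effect. This is a fair reason to report new-onset changes. But the endpoint does not say new onset, and it lists baseline among its assessments. Reporting children in range at screening as a separate group meets both aims.
- **Worsening is visible elsewhere.** Section 9.1 counts abnormal laboratory findings and exacerbations as adverse events. By-visit summaries include the maximum, and values are listed by subject, which for 32 children can be read by hand. Section 9.10 requires repeat tests and liver-event pages at 3 times screening, and stops the device at 8 times. This stands. A reader might infer that the safety analysis misses worsening from an abnormal baseline, and the documents do not support that.
- **The rule does not say normal at baseline.** A reader might infer that a child abnormal at screening can never be counted. The wording does not go that far: a child who returns to range and then leaves it again has made a normal-to-abnormal change. The gap concerns children who stay out of range.
- **Table layouts belong in the statistical analysis plan, which is not at hand.** This is true of layout. But the protocol has itself fixed an incidence rule, twice, and that rule differs from its endpoint. No endpoint promises a tally of the section 9.10 limits, so the lack of one contradicts nothing; adding it is an improvement.

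**Conclusion.** The point holds in a limited form. The stated laboratory incidence rule is narrower than the stated endpoint. It omits any child who is out of range at screening and remains so, whatever the degree of worsening, and its denominator is not settled.

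The size is unknown. It depends on how many children enter out of range on each parameter, which the protocol does not report. The 40-60% figure in the background should not be used to fill that gap: it concerns infants, and it is a liver disease rate rather than an ALT rate. The table in the working shows direction only.

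The consequence is confined to how the laboratory safety result is reported. No efficacy conclusion, stated precision figure or on-study protection changes. It is worth correcting because safety is a stated objective, there is no comparator and the correction is nearly free.

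The synopsis and body also differ on direct bilirubin at entry: criterion 6 in the synopsis joins its two conditions with *and*, criterion 7 in the body with *or*. That is a separate eligibility matter, and this point does not depend on it. Even on the synopsis wording, other parameters may be out of range at screening.

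**What to change.** In section 10.2.3 and the synopsis statistical methods:

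- Replace the normal-to-abnormal count with a shift table for each parameter: baseline category (low, normal or high by the hospital's range) against worst post-baseline category.
- State the denominator: all treated children with a post-baseline value for that parameter and, separately, those in range at screening. The second group gives the new-onset rate.
- Add the number and percentage of children whose ALT or AST exceeds 3, 5 and 8 times the screening value, since a rise from high to higher stays in one cell of the shift table.
- Keep the listing by subject.

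The cost is a wording change in two places and a few extra tables. The laboratory samples are already scheduled at screening and at Days 7, 14, 28, 60 and 90, so no new data are needed. The reported laboratory incidence may look less favourable than under the present rule.
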